## Abstract

**Background:**

Hyperopia occurs due to insufficient ocular growth and a failure to emmetropize in childhood. In anisohyperopia, it is unclear why one eye may remain hyperopic while the fellow eye grows toward an emmetropic state. Animal studies have shown that manipulating peripheral defocus through optical means while simultaneously providing correct axial focus can either discourage or encourage axial eye growth to effectively treat myopia or hyperopia, respectively. Myopia progression and axial eye growth can be significantly reduced in children and adolescents through the use of multifocal contact lenses. These contact lenses correct distance central myopia while simultaneously imposing relative peripheral myopic defocus. The effect of correcting distance central hyperopia while simultaneously imposing relative peripheral hyperopic defocus is yet to be elucidated in humans.

**Objective:**

The objective of our study is to understand the natural progression of axial eye growth and refractive error in hyperopes and anisohyperopes and to establish whether axial eye growth and refractive error can be modified using multifocal contact lenses in hyperopes and anisohyperopes.

**Methods:**

There are 3 elements to the program of research. First, the natural progression of axial eye growth and refractive error will be measured in spectacle-wearing hyperopic and anisohyperopic subjects aged between 5 and <20 years. In other words, the natural growth of the eye will be followed without any intervention. Second, as a paired-eye control study, anisohyperopes aged between 8 and <16 years will be fitted with a center-near multifocal design contact lens in their more hyperopic eye and a single-vision contact lens in the fellow eye if required. The progression of axial eye growth and refractive error will be measured and compared. Third, subjects aged between 8 and <16 years with similar levels of hyperopia in each eye will be fitted with center-near multifocal design contact lenses in each eye; the progression of axial eye growth and refractive error in these subjects will be measured and compared with those of subjects in the natural progression study.

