**Conclusions:**

This trial will establish whether axial eye growth can be accelerated in children with hyperopia by imposing relative peripheral hyperopic defocus using center-near multifocal contact lenses.

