For the study, healthy hyperopic children and adolescents will be recruited via the researchers’ optometry practices and Aston University's Eye Clinic. A database search will be performed by the immediate research team to identify potential participants who meet the criteria for inclusion; these individuals will be contacted via post with information regarding the study and how to participate. A poster will also be displayed at both research venues as a means of recruiting other potential participants. Contact details will be stated on the poster to enable anyone interested in joining the study to contact the researcher for further details.

All participants, including parent(s) or guardian(s), expressing an interest in joining the study or wishing to recruit their child into the study will be provided detailed information regarding the study and will have the opportunity to ask questions before completing the consent form declaration.

Allocation to the contact lens-wearing and the natural progression arms of the study will not be randomized. Individuals who are willing and able to use contact lenses will be given the opportunity to be included in the contact lens arm of the study; those who do not want to wear, are unable to handle, or unsuitable for contact lenses will be given the opportunity to participate in the natural progression arm of the study.

After obtaining informed consent, all participants will undergo a number of visual assessments including a background questionnaire, axial length measures, subjective refraction, accommodative lag, amplitude of accommodation, stereopsis, vision and visual acuity, postcycloplegic objective refraction, postcycloplegic peripheral refraction at 30**°** temporally and nasally, and 20**°** superiorly and inferiorly, and pupil size.

For the natural progression study, the normal growth of the eyes will be followed at 7 visits over 3 years without any intervention. A topical cycloplegic (cyclopentolate hydrochloride 1%) will be used on visits 1, 2, 4, 6, and 7 (Table 1).

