### Inclusion Criteria

To be included in the study, the participants had to be aged between 5 and <20 years at the initial examination for the natural progression study and between 8 and <16 years at the initial examination for the intervention study. Furthermore, the parents must have read, understood, and signed the informed consent form, and the participants must have read, understood, and signed the assent form. The participants in the intervention groups had to agree to wear the prescribed contact lenses for a minimum of 10 hours per day, at least 6 days per week, for the 2-year duration of the intervention period and be in good general health with no contraindications to contact lens wear. Additionally, the following criteria had to be met: maximum manifest spherical refractive error of +6.00 D, maximum manifest cylindrical refractive error of −1.00 D, minimum anisometropia of >1.00 D in the anisohyperopic group (mean spherical error), maximum anisometropia of 1.00 D in the nonanisohyperopic group (mean spherical error), and minimum mean spherical refractive error of +2.00 D in the more hyperopic eye. Furthermore, participants had to be competent at handling contact lenses and understand the instructions provided to ensure safe wear.

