### Statistical Analyses

All data will be analyzed using the commercially available software SPSS version 23 (IBM, NY, United States) using a repeated-measures mixed analysis of variance design with 1 between-subject factor and 1 within-subject factor. Principal outcomes measures are: change in axial eye growth and change in refractive error.

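### The hyperopic lens arm (8 to <16 years) is compared, with no age term in the model, with a self-selected control arm aged 5 to <20 years that includes anisohyperopes, so age-related growth may hide or mimic a lens effect

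*Protocol article*

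**What the plan says.** The Methods part of the protocol article's abstract describes the treated group: "subjects aged between 8 and <16 years with similar levels of hyperopia in each eye will be fitted with center-near multifocal design contact lenses". Their outcomes will be "measured and compared with those of subjects in the natural progression study", with no subset of that study named. The same paragraph describes the natural progression study as following "spectacle-wearing hyperopic and anisohyperopic subjects aged between 5 and <20 years".

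Inclusion Criteria repeats the two age ranges: participants had to be "aged between 5 and <20 years at the initial examination for the natural progression study and between 8 and <16 years" for the intervention study. It also caps anisometropia at 1.00 D in the nonanisohyperopic group.

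Study Design states: "Allocation to the contact lens-wearing and the natural progression arms of the study will not be randomized". The natural progression arm is offered to "those who do not want to wear, are unable to handle, or unsuitable for contact lenses".

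Statistical Analyses gives one method for all data, a "repeated-measures mixed analysis of variance design with 1 between-subject factor and 1 within-subject factor". The principal outcomes are changes in axial growth and in refractive error. The abstract's Conclusions say: "This trial will establish whether axial eye growth can be accelerated in children with hyperopia".

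**The concern.** The two groups differ by design in three ways that could bear on growth: eligible age, the presence of anisohyperopes, and the route of entry. Ability to handle lenses plausibly depends on age, so the route of entry may widen the age difference. If growth rate changes with age, a control arm weighted towards one end of its range would differ from the lens arm even if the lenses did nothing. Controls that grow faster on that account would mask a lens effect, and controls that grow more slowly would create an apparent one.

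The article names the comparator and fixes the number of factors in the model. Taken as group and time, those two factors leave no term for age or baseline measurements. What is at stake is the only between-group comparison described for the hyperopic arm, on both principal outcomes.

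**Working it through.** **No plan figure to reproduce.** Sample Size gives alpha .05, 80% power and an unspecified attrition allowance. It gives no N, effect size, SD or age distribution.

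**1. Age overlap (Inclusion Criteria).** Control span 20 − 5 = 15 years; treated span 16 − 8 = 8 years. Control years without a treated counterpart: (8 − 5) + (20 − 16) = 7, and 7/15 = 47%. Range midpoints are (5 + 20)/2 = 12.5 and (8 + 16)/2 = 12.0 years, a gap of 0.5 years.

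**2. Bias in mm over 24 months of lens wear.** Assume growth slows linearly by b mm/yr per year of age, with mean age gap D:

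bias = 2 × b × D

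| b (assumed) | D (assumed) | bias |
|---|---|---|
| 0.005 | 0.5 y | 0.005 mm |
| 0.01 | 0.5 y | 0.01 mm |
| 0.01 | 2 y | 0.04 mm |
| 0.02 | 3 y | 0.12 mm |

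**3. False-positive rate with no lens effect.** A two-sided two-sample t-test at 0.05 stands in for the group contrast. Let s be the age slope in SDs of growth per year of age and n the number per arm. The noncentrality is s × D × √(n/2) on 2n − 2 degrees of freedom. For example, n = 30, s = 0.1 and D = 2 give 0.2 × √15 = 0.775 and a rate of 0.119. With n = 30 and s from 0.05 to 0.20 (all assumed):

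| D | rate |
|---|---|
| 0.5 y | 0.05–0.07 |
| 1 y | 0.05–0.12 |
| 2 y | 0.07–0.33 |
| 3 y | 0.09–0.63 |

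At D = 3 the range is 0.07–0.36 with 15 per arm and 0.13–0.90 with 60 per arm.

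**4. Do similar midpoints settle it?** Suppose growth decays as exp(−k(age − 5)) with k from 0.05 to 0.30 per year (assumed) and ages are uniform between limits a and c. Mean growth is then [exp(−k(a − 5)) − exp(−k(c − 5))] / [k(c − a)]. The ratio of control to treated growth with no lens effect is:

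- controls uniform over 5 to 20: 0.99 to 1.43 (at k = 0.2, 0.317/0.274 = 1.16);
- controls uniform over 5 to 12: 1.19 to 2.71;
- controls uniform over 14 to 20: 0.78 down to 0.20.

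Ratios above 1 hide a lens effect and ratios below 1 imitate one. Close midpoints therefore do not guarantee balance, and the direction depends on who enrolled.

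**5. Data for a remedy.** Tables 1 and 2 schedule axial length and postcycloplegic refraction at visits 1 and 2 in every arm. In the intervention arms, lenses are fitted at visit 2. Pre-lens values and six months of pre-lens growth are therefore available in both groups.

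**The case against.** **The article is a condensed account.** The comparator subset and covariates are often left to a fuller document, and counting factors does not say who enters each comparison. Restriction would be compatible with the stated model. This carries weight for restriction but less for adjustment: the two-factor ANOVA is stated for all data, and adding a covariate changes it.

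**Change outcomes and the run-in give some protection.** Analysing change removes differences in baseline level. It does not remove differences in growth rate unless pre-lens growth is used, and the analysis section does not say that it is.

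**The bias may be small.** The 47% describes eligibility, not enrolment. With a 0.5-year gap the linear calculation gives only 0.01 mm and a false-positive rate near nominal. This stands: the size is undetermined.

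**The wide control range is legitimate.** It serves the natural-history aim and is not itself an error.

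**Stronger readings that a reader might infer.** One is that the comparison is known to be biased, because the youngest controls grow fastest and the oldest have nearly stopped growing. The article gives no age slope for hyperopes, and measuring natural growth in them is one of its aims. Another is that the trial as a whole cannot support its conclusion. That conclusion also draws on the anisohyperopic paired-eye comparison, where both eyes share the same age.

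**Conclusion.** The concern holds for the hyperopic-arm comparison. As written, it sets treated children against a broader, self-selected and partly anisohyperopic group, using a model with no term for age. Confounding by age is possible and the stated analysis would not remove it.

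Its size and direction cannot be fixed from the document. Under the assumed linear slopes and gaps of 0.5 to 3 years it runs from 0.005 to 0.12 mm over 24 months. The slopes, gaps and arm sizes are all assumptions. The overlap arithmetic, the mixed comparator, the non-random allocation and the two-factor model rest on the text itself.

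**What to change.** For the hyperopic intervention comparison:

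- Restrict the comparator to natural progression participants aged 8 to <16 years at visit 1 with anisometropia of 1.00 D or less.
- Replace the unadjusted ANOVA with a repeated-measures model adjusting at least for age and for visit 2 (pre-lens) axial length and cycloplegic refraction. Use growth between visits 1 and 2 as a further covariate or in a sensitivity analysis.
- Describe the result as an adjusted non-randomised comparison wherever the hyperopic-arm finding is stated.

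Keep the full 5 to <20 cohort for the natural-history aim, and leave the paired-eye comparison as it is.

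No new visits or measurements are needed. The cost is fewer controls in this comparison and a more modest claim. The effect on power cannot be computed without N, SD and the age distribution. Adjustment deals with age only if age is modelled adequately, and self-selection on unmeasured factors remains.

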**Results:**

Recruitment commenced on 6 June 2016 and was completed on 8 April 2017. We estimate the data collection to be completed by April 2020.

**Conclusions:**

This trial will establish whether axial eye growth can be accelerated in children with hyperopia by imposing relative peripheral hyperopic defocus using center-near multifocal contact lenses.

**Trial Registration:**

ClinicalTrials.gov NCT02686879; https://clinicaltrials.gov/ct2/show/NCT02686879 (Archived by Webcite at http://www.webcitation.org/71o5p3fD2)

**Registered Report Identifier:**

RR1-10.2196/9320

## Introduction

### Background

Uncorrected hyperopia can cause blurring of distance vision and near vision and is a known risk factor for the development of strabismus and amblyopia [1]. There is a growing body of evidence that uncorrected hyperopia, in addition to visual consequences, may have a negative impact on educational attainment [2,3] and visuocognitive and visuomotor skills [4]. Hyperopia has received much less attention from research than myopia even though the impact of moderate to high levels of hyperopia, especially in one eye (anisohyperopia), can lead to amblyopia if not fully corrected at a young age [5]. Hyperopia occurs as a consequence of insufficient ocular growth and a failure to emmetropize in childhood, with the majority of hyperopic refractive errors resulting from an eye that is too short for its refractive power [6]. In anisohyperopia, it is unclear why one eye may remain hyperopic while the fellow eye grows toward an emmetropic state. Myopic eyes typically exhibit relative hyperopic blur in the periphery [7,8], which is thought to be a precursor of the development of myopia [9]. Studies on animals have suggested that manipulating peripheral defocus through optical means while simultaneously providing correct axial focus can either discourage or encourage axial eye growth to effectively treat myopia or hyperopia, respectively [10].

It has been established that myopia progression and axial eye growth can be significantly reduced in children and adolescents through the use of bifocal or dual-focus contact lenses [11-13]. These contact lenses are designed to correct distance central myopia while simultaneously imposing relative peripheral myopic defocus. This intervention relies on active accommodation, and the myopia control studies have shown that children accommodate normally with multifocal contact lenses [11]. In contrast to the myopic eye, the hyperopic eye tends to exhibit relative peripheral myopia [8].

This study explores the use of center-near multifocal design contact lenses to correct distance central hyperopia while simultaneously imposing relative peripheral hyperopic defocus. The aim is to determine, for the first time, whether axial eye growth can be accelerated in children with hyperopia and anisohyperopia to reduce the refractive error and improve visual outcome.

### Study Objectives

The objectives of our study are to understand the natural progression of axial eye growth and refractive error in hyperopes and anisohyperopes, and to establish if axial eye growth and refractive error can be modified using center-near multifocal design contact lenses in hyperopes and anisohyperopes to improve visual outcome.

## Methods

### Study Design

There will be 3 elements to the proposed program of research:

*Natural progression*: Refractive error and axial eye growth will be followed over a 3-year period in hyperopic and anisohyperopic participants aged between 5 and <20 years to gain an understanding of the natural progression of these parameters in the specified cohort. This arm of the study does not involve an intervention.*Hyperopic intervention*: For this part of the study, refractive error and axial eye growth will be followed in participants aged between 8 and <16 years over a 6-month period, after which the participants will wear bifocal soft contact lenses daily for 2 years. The intervention will then be withdrawn before the final data collection point 6 months later. The center-near design contact lenses will provide clear central vision at both distance and near, thus, exposing the retina to peripheral hyperopic defocus from the distance zone.*Anisohyperopic intervention:* Anisometropes represent a unique example of ocular development, where the two eyes of an individual, with an identical genetic background and seemingly subject to identical environmental influences, can grow asymmetrically to produce significantly different refractive errors. Axial eye growth and refractive error will be followed in participants aged between 8 and <16 years over a 6-month period before being fitted with a center-near design bifocal soft contact lens in their more hyperopic eye, while the fellow eye will be fitted with a single-vision contact lens if required. The contact lenses will be worn daily for 2 years. The intervention will then be withdrawn before the final data collection point 6 months later. If and when the refractive error in the more hyperopic eye has reached a level similar to that in the less hyperopic eye (<0.25 diopter [D] interocular difference), both eyes will be fitted, if necessary, with bifocal center-near design contact lenses in line with the protocol for participants in the hyperopic intervention group.

For the study, healthy hyperopic children and adolescents will be recruited via the researchers’ optometry practices and Aston University's Eye Clinic. A database search will be performed by the immediate research team to identify potential participants who meet the criteria for inclusion; these individuals will be contacted via post with information regarding the study and how to participate. A poster will also be displayed at both research venues as a means of recruiting other potential participants. Contact details will be stated on the poster to enable anyone interested in joining the study to contact the researcher for further details.

All participants, including parent(s) or guardian(s), expressing an interest in joining the study or wishing to recruit their child into the study will be provided detailed information regarding the study and will have the opportunity to ask questions before completing the consent form declaration.

Allocation to the contact lens-wearing and the natural progression arms of the study will not be randomized. Individuals who are willing and able to use contact lenses will be given the opportunity to be included in the contact lens arm of the study; those who do not want to wear, are unable to handle, or unsuitable for contact lenses will be given the opportunity to participate in the natural progression arm of the study.

After obtaining informed consent, all participants will undergo a number of visual assessments including a background questionnaire, axial length measures, subjective refraction, accommodative lag, amplitude of accommodation, stereopsis, vision and visual acuity, postcycloplegic objective refraction, postcycloplegic peripheral refraction at 30**°** temporally and nasally, and 20**°** superiorly and inferiorly, and pupil size.

For the natural progression study, the normal growth of the eyes will be followed at 7 visits over 3 years without any intervention. A topical cycloplegic (cyclopentolate hydrochloride 1%) will be used on visits 1, 2, 4, 6, and 7 (Table 1).

Participants in the intervention arms of the study will also have the normal growth and visual characteristics of the eyes followed at 7 visits over 3 years. In addition, they will have their suitability for contact lens wear determined at the second visit, 6 months after the first visit, which will require instructions on contact lens wear and follow-up appointments. In total, for participants in the intervention arms of the study, there will be 9 scheduled visits, with a cycloplegic used on visits 1, 2, 6, 8, and 9 (Table 2). There may be unscheduled visits if any problems arise as a result of contact lens wear. The participants, with parental support where necessary, will be instructed on how to insert, remove, and care for their contact lenses.

**Table 1 table1:** Procedures for participants in the natural progression arm of the study.

Procedure	Visit 1 (month 1)	Visit 2 (month 6)	Visit 3 (month 12)	Visit 4 (month 18)	Visit 5 (month 24)	Visit 6 (month 30)	Visit 7 (month 36)
Informed consent	✓	✓	✓	✓	✓	✓	✓
Questionnaire	✓	✓	✓	✓	✓	✓	✓
Axial length	✓	✓	✓	✓	✓	✓	✓
Subjective refraction	✓	✓	✓	✓	✓	✓	✓
Accommodative lag	✓	✓	✓	✓	✓	✓	✓
Amplitude of accommodation	✓	✓	✓	✓	✓	✓	✓
Stereopsis	✓	✓	✓	✓	✓	✓	✓
Vision and visual acuity	✓	✓	✓	✓	✓	✓	✓
Postcycloplegic refraction	✓	✓		✓		✓	✓
Peripheral refraction	✓	✓		✓		✓	✓

**Table 2 table2:** Procedures for participants in the intervention arms of the study.

Procedure	Visit 1 (month 1)	Visit 2 (month 6)	Visit 3 (month 7)	Visit 4 (month 8)	Visit 5 (month 12)	Visit 6 (month 18)	Visit 7 (month 24)	Visit 8 (month 30)	Visit 9 (month 36)
Informed consent	✓	✓			✓	✓	✓	✓	✓
Questionnaire	✓	✓			✓	✓	✓	✓	✓
Axial length	✓	✓			✓	✓	✓	✓	✓
Subjective refraction	✓	✓			✓	✓	✓	✓	✓
Accommodative lag	✓	✓			✓	✓	✓	✓	✓
Amplitude of accommodation	✓	✓			✓	✓	✓	✓	✓
Stereopsis	✓	✓			✓	✓	✓	✓	✓
Vision and visual acuity	✓	✓			✓	✓	✓	✓	✓
Postcycloplegic refraction	✓	✓				✓		✓	✓
Peripheral refraction	✓	✓				✓		✓	✓
Pupil size					✓				
Contact lens fitting		✓							
Contact lens aftercare			✓	✓	✓	✓	✓	✓	

For the anisohyperopes, the more hyperopic eye will be fitted with a commercially available soft multifocal contact lens and the less hyperopic eye will be fitted with a soft single-vision contact lens, if required. Participants with similar levels of hyperopia in each eye will be fitted with commercially available soft multifocal contact lenses in both eyes.

For anisohyperopic subjects, if the level of hyperopia in the more hyperopic eye reduces to a level which is similar to that of the less hyperopic eye, both eyes will be fitted with multifocal contact lenses if sufficient hyperopia remains, in line with the inclusion criteria for the second arm of the study.

For nonanisohyperopic subjects, the intervention will be stopped when the refractive error has reached a mean spherical error of +0.50 D. At the end of an intervention period of 24 months, contact lens wear will cease and the participants will be assessed for the final time after an interval of 6 months.

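### In the paired-eye study the control eye may be given the multifocal lens once the eyes converge; the stated ANOVA does not represent this switch, so the end-of-wear contrast is attenuated

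*Protocol article*

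**What the plan says.** The Methods part of the Abstract describes the anisohyperopic element this way: "as a paired-eye control study, anisohyperopes aged between 8 and <16 years will be fitted with a center-near multifocal design contact lens" in the more hyperopic eye. The fellow eye, with a single-vision lens if it needs one, is the comparator.

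Study Design then gives a rule for changing the comparator, which applies once the treated member of the pair "has reached a level similar to that in the less hyperopic eye (<0.25 diopter [D] interocular difference), both eyes will be fitted, if necessary". The lens meant is the multifocal design. Later in the same section the rule returns with a different condition: "both eyes will be fitted with multifocal contact lenses if sufficient hyperopia remains, in line with the inclusion criteria for the second arm". In the order used by Study Design, the second arm is the hyperopic intervention; the Abstract lists the elements in another order.

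Inclusion Criteria require "minimum anisometropia of >1.00 D in the anisohyperopic group (mean spherical error") and at least +2.00 D in the more hyperopic eye. Statistical Analyses applies to the data a "repeated-measures mixed analysis of variance design with 1 between-subject factor and 1 within-subject factor", with change in axial growth and change in refractive error as principal outcomes. No primary time point is named.

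**The concern.** The fellow eye is the only within-child control in a study whose other comparison is not randomised. A child whose eyes converge may lose that control, and the event that removes it is a good result on one of the two principal outcomes. From that visit both eyes can wear the same lens, so further change in the two eyes no longer measures the lens effect.

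A repeated-measures ANOVA with one between-subject and one within-subject factor cannot express a control eye that becomes a treated eye part-way. Keeping the later visits under the initial allocation dilutes the contrast. Setting them to missing leaves incomplete rows, which classical repeated-measures ANOVA discards, so the converging children leave the analysis altogether. Both routes understate a real effect.

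**Working it through.** The article states no sample size, effect size, SD or attrition rate, so there is no figure of its own to reproduce.

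**Inputs from the protocol article.** Baseline interocular difference A0 above 1.00 D, at least +2.00 D in the more hyperopic eye, maximum sphere +6.00 D (Inclusion Criteria). Switch threshold 0.25 D and 2 years of wear (Study Design), which Table 2 places between months 6 and 30. Subjective refraction at months 12, 18 and 24, that is after 0.5, 1 and 1.5 years of wear. Between fitting and month 30, cycloplegic refraction is done only at month 18 (Table 2).

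**Step 1: what convergence requires.** Let r be the differential change between eyes in D/year. The gap reaches 0.25 D after t = (A0 − 0.25)/r years, so convergence within 2 years needs r above (A0 − 0.25)/2:

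- A0 = 1.00 D: 0.75/2 = 0.375 D/year
- A0 = 1.50 D: 1.25/2 = 0.625 D/year
- A0 = 2.00 D: 1.75/2 = 0.875 D/year

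**Step 2: what a switched child loses.** Without a switch, the between-eye difference in change at the end of wear is 2r. If the eyes change alike after the switch, it stays at r·t, so the share kept is t/2: 0.5/2 = 25% for a switch at month 12, 1/2 = 50% at month 18, and 1.5/2 = 75% at month 24.

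**Step 3: effect on the group mean.** This needs a simulation (400,000 draws) with assumptions that are not in the documents: A0 uniform from 1 to 2 D, more hyperopic eye uniform from +2 to +6 D (draws with a fellow eye below 0 D dropped), r normal with SD 0.2 D/year, measurement error SD 0.25 D on the difference, and no differential change after the switch. The residual condition is taken as at least +2.00 D remaining in the more hyperopic eye.

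| Mean r (D/year) | Contrast without switch (D) | Checks at months 12/18/24: switched, contrast, loss | Same, with residual condition: loss | Month-18 check only: loss | Month-18 check and residual condition: loss |
|---|---|---|---|---|---|
| 0.3 | 0.60 | 6%, 0.58 D, 3% | 3% | 1% | 1% |
| 0.5 | 1.00 | 17%, 0.93 D, 7% | 6% | 3% | 2% |
| 0.75 | 1.50 | 42%, 1.26 D, 16% | 12% | 8% | 6% |

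With A0 from 1 to 3 D the losses are about half of these. Switchers have larger true effects on average: 0.56 against 0.30, 0.68 against 0.50, and 0.86 against 0.75 D/year.

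**Step 4: dropping the switchers instead.** The mean among the remaining children is (overall mean − share switched × switchers' mean)/(1 − share switched). For the second to fourth columns of results above, using the first check schedule:

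- r = 0.3: (0.300 − 0.056 × 0.559)/0.944 = 0.285, a loss of 5%
- r = 0.5: (0.500 − 0.168 × 0.684)/0.832 = 0.463, a loss of 7%
- r = 0.75: (0.750 − 0.418 × 0.861)/0.582 = 0.670, a loss of 11%

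Dropping is therefore also biased toward no effect.

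**Cross-check under other assumptions.** Take A0 as 1.00 D plus an exponential excess of scale 0.5 D, a 24-month effect with mean 0.50 D (SD 0.4) or 0.80 D (SD 0.5), error SD 0.25 × √2 = 0.354 D on the difference, the same three checks and no residual condition. Then 10% or 21% switch, the loss is 7% or 12%, and dropping switchers costs 9% or 14%. The direction, and growth with the true effect, agree with Step 3.

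**The case against.** The strongest reply is that this is a condensed article. Statistical Analyses names a model family, software and outcomes. It does not say which visits enter, how switched children are coded, or that month 30 is the primary contrast; month 30 is used here only because lens wear ends then. A full protocol or SAP may deal with the switch. That is fair, and missing detail alone would be no finding. What stands is that the text itself fixes an outcome-dependent change of the comparator and pairs it with a model that cannot represent it, whichever visits are kept.

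A reader might also infer more than the documents support:

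- *Every converging child is switched.* No. One passage adds a necessity condition and the other requires enough remaining hyperopia.
- *After a switch the comparison is worthless.* No. The outcome is change, so the difference gained before the switch is retained, as Step 2 shows.
- *Switchers are exactly the best responders.* Too strong. A small baseline difference and measurement error also select, although switchers do better on average.
- *Measurement noise alone triggers many switches.* The article does not say which refraction decides, or that one reading suffices. Any rate depends on an assumed course of the gap.
- *The rule for non-anisohyperopic children, that "the intervention will be stopped when the refractive error has reached a mean spherical error of +0.50 D", is the same flaw.* Stopping at that level belongs to the stated regimen, and keeping those children in their group is a sound main analysis. It also takes at least 2.00 − 0.50 = 1.50 D of change to get there. It is not a main point here.

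Finally, the bias is toward no effect, so it cannot create an apparent benefit.

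**Conclusion.** The concern holds as attenuation of the paired contrast, not as its loss. The switch depends on a principal outcome, tends to take better responders, and is not represented by the stated ANOVA. The loss in the mean end-of-wear contrast is roughly 1–3% if the differential effect is 0.3 D/year and up to about 16% at 0.75 D/year.

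These figures rest on assumed effect sizes, SDs, measurement error and baseline distribution, and on no differential change after the switch. They fall if the residual-hyperopia condition applies, if only the month-18 cycloplegic visit can trigger the switch, or if baseline anisometropia is wider. Severity is moderate: the distortion is modest at plausible small effects, but it grows with the effect the study hopes to find, and it falls on the only within-child comparison.

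**What to change.** 1. Record for each child the switch date, and the refraction (type and value) on which it was decided.
2. For the paired contrast, use both eyes' data up to and including the visit at which the switch is decided, in a likelihood-based mixed model instead of classical repeated-measures ANOVA.
3. Include the triggering refraction in the model. Ignorability of the switch depends on this: if subjective refraction triggers and cycloplegic refraction is analysed, both are needed. For axial length, model it jointly with refraction or carry refraction as an auxiliary outcome.
4. Report post-switch data separately, and give the all-visits analysis as a sensitivity analysis.
5. Name the time point of the paired contrast.
6. Reconcile the two Study Design statements of the switch condition, including which arm's criteria are meant. Which condition should apply is for the investigators.

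The cost is analysis-plan wording and one extra recorded item, with no change to lens care. The downside is that end-of-wear estimates for switchers rest on a missing-at-random extrapolation, with slightly wider intervals.
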